## Data collection and management

### Plans for assessment and collection of outcomes {18a}

At baseline and during each follow-up, researchers will provide paper-based questionnaires for guardians to complete, and the results will be entered into a spreadsheet for analysis. All other clinical assessments will be performed by experienced clinicians using relevant measuring instruments (as specified in item 12). Measurements will be repeated to ensure the reliability and validity of the data collection. Meanwhile, patients’ general information, medical history, baseline and follow-up results, adverse event reports, and trial summaries will be recorded in the CRFs by researchers on time. All researchers and clinicians will undergo training on participant recruitment, assessment, intervention, and data backup before participating in the study.

Cycloplegic autorefraction will be performed using the Topcon KR800 autorefractor unit following the cycloplegia regimen of 1% cyclopentolate (Cyclogyl, AlconConvreur). The procedure involves administering two drops of 1% cyclopentolate separated by a 5-min interval, followed by a 30-min resting period after the final instillation. Complete cycloplegia is confirmed by the absence of fluctuation in retinoscopy findings under cycloplegic conditions in children or by performing autorefraction combined with careful subjective refraction. Spherical equivalent is calculated as spherical power plus half of the cylinder power. Cycloplegic measurements will be performed at baseline, the 6-month follow-up, and the 12-month follow-up to assess the primary outcome.

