### Plans to promote participant retention and complete follow-up {18b}

To ensure high participant retention and complete follow-up throughout the study, a comprehensive strategy will be implemented. This strategy will focus on maintaining participant engagement, minimizing dropout rates, and addressing potential challenges that may arise during the study.

Engagement and retention strategies
Regular communication: Participants will be regularly contacted via phone calls, text messages, or mobile applications to provide reminders of upcoming appointments and to maintain engagement.Flexible scheduling: Follow-up visits will be scheduled at times convenient for the participants and their families, such as weekends and holidays.Incentives: To further encourage retention, participants will receive small incentives, such as gift cards or study-related materials, upon completion of key milestones (e.g., baseline, 6-month, and 12-month visits).

2.Handling withdrawals or treatment modifications

In the event that a participant decides to withdraw or is unable to complete the study, their outcome data up to the point of withdrawal will be collected. This ensures that even if they do not complete the entire study, the data they have contributed remains valuable.Reasons for withdrawal: Participants who withdraw will be asked to provide the reason for their decision (e.g., personal, logistical, or health-related issues), which will be documented for further analysis and to inform potential improvements in future studies.Changes in treatment plan: If participants need to switch to an alternative treatment, the research team will collect relevant outcome data before the change is made, ensuring that the participant’s previous data remains part of the analysis. This will allow the study to account for the impact of treatment changes on the outcomes.

3.Follow-up and data collection

In the event of missing data or uncompleted follow-up visits, efforts will be made to contact participants to reschedule and collect the necessary data. If a participant cannot be reached for any follow-up visit, the last available data will be included in the analysis, and the participant will be considered as missing for subsequent follow-up points.

By employing these strategies, we aim to minimize participant dropout, ensure high-quality follow-up data, and maximize the retention of participants throughout the 1-year study period.

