## Statistical methods

### Statistical methods for primary and secondary outcomes {20a}

Analysis of primary outcomeIn this participant-based study, the primary outcome is the proportion of myopia onset. This outcome is measured as a binary (nominal) variable. Participants are classified as either having experienced the onset of myopia (Yes) or not (No), based on whether their cycloplegic spherical equivalent refractive error reaches or exceeds − 0.50 D in either eye at the 1-year follow-up. This is a single endpoint measure, assessed once at the end of the 1-year follow-up period. It provides a proportion of participants who experience the onset of myopia. To test the effectiveness of DIST on the primary outcomes, logistic regression including trend analysis will be used, which can both examine the overall relationship and detect potential trends related to different treatments. In addition, covariates such as baseline spherical equivalent refractive error, age, gender, and study group (Intervention vs. Control) will be included to ensure a parsimonious logistic regression model while controlling for factors known to influence myopia onset and progression.The primary analysis will be conducted on the ITT population, which is defined as all randomized participants with at least one post-baseline measurement. For all analyses, the underlying model assumptions will be rigorously evaluated. For instance, when applying logistic regression to assess the binary primary outcome, we will verify the linearity of the logit for continuous covariates using methods such as the Box–Tidwell test, assess multicollinearity via variance inflation factors (VIF), and examine residuals and influence statistics (e.g., Cook’s distance) to identify any influential outliers. Missing data will be addressed using multiple imputations by chained equations under the assumption of data missing at random (MAR), with sensitivity analyses planned to assess the impact of outliers, nonadherence, and loss to follow-up.Analysis of secondary outcomesThe secondary outcomes are intended to capture aspects of the intervention effect that are not fully reflected by the primary outcome. For example, even if the primary outcome (myopia onset) does not show a statistically significant difference, significant changes in spherical equivalent or axial length may still be observed, thereby indicating a potential benefit of the intervention in slowing myopia progression.For the three secondary outcomes: (1) the proportion of fast progressors over 1 year, (2) changes in spherical equivalent progression, and (3) changes in AL (mm) at each follow-up point, the following statistical procedures will be employed:Proportion of fast progressors (binary outcome)This endpoint will be analyzed using logistic regression. The model will estimate the odds of being classified as a fast progressor over 1 year, comparing the intervention group to the control group. Covariates to be included in the model are baseline spherical equivalent refractive error (continuous), age (continuous), and gender (categorical), as these factors have been shown in prior research to influence myopia progression. The study group (intervention vs. control) will be the primary factor of interest. These covariates are selected based on their theoretical relevance and empirical support, ensuring a parsimonious model that controls for potential confounding without overfitting.Changes in spherical equivalent progression (continuous outcome)The change in spherical equivalent progression over time will be analyzed using a repeated measures mixed-effects model. This model will account for within-subject correlations across multiple follow-up points and will include fixed effects for the treatment group, time (as a categorical or continuous variable depending on the observed pattern), and the interaction between treatment and time. Baseline spherical equivalent refractive error, age, and gender will be included as covariates to adjust for initial differences and known predictors of refractive change. The rationale for these covariates is their established association with myopia progression, ensuring that the model is both explanatory and parsimonious. Model selection procedures, such as stepwise backward elimination based on the Akaike Information Criterion (AIC) or likelihood ratio tests, will be applied to refine the final model.Changes in AL (mm)Similar to the spherical equivalent endpoint, changes in axial length (measured in mm) at each follow-up will be analyzed using a repeated measures mixed-effects model or an analysis of covariance (ANCOVA) for longitudinal data. The model will include fixed effects for treatment, time, and their interaction. Covariates will include baseline axial length, baseline spherical equivalent, age, and gender. These factors are chosen because they are known to influence ocular growth and, consequently, axial elongation. As with the other endpoints, a parsimonious model will be achieved by using stepwise selection methods or likelihood ratio tests to retain only covariates that contribute significantly to explaining the variation in axial length change.The results of these analyses will be presented as adjusted odds ratios with 95% confidence intervals for the binary outcome and as least-squares means (LSMEANS) with standard errors for the continuous outcomes. In addition, p-values will be reported to assess the statistical significance of the observed differences between intervention groups.Analysis of exploratory outcomesTime-to-myopia onset analysisFor comparing the time to myopia onset (time-to-event outcome) among 3 treatment groups, we all create a number-at-risk table and use the Kaplan–Meier method to estimate survival curves, followed by the log-rank test to assess differences statistically.Myopia onset associationsA logistic regression model will be built with myopia onset as the dependent variable and near-work duration, device usage duration, and confounding factors as independent variables. The near-work duration was derived from the near-work log cards and questionnaires, with the daily averages taken for analysis. Odds ratio (OR) and its 95% confidence interval will be estimated to determine associations while controlling for confounding.Dose–response relationship analysisWe will group near work and device usage durations (e.g., by quartiles). Use the Cochrance–Armitage trend test to analyze if there’s a dose–response relationship. Curve fitting (such as polynomial regression) can also be used to further explore the non-linear relationship between them.Choroidal thickness changesFor exploring changes in choroidal thickness during different follow-up periods among three groups, repeated measures analysis of variance (ANOVA) will be used. If significant effects are found, post hoc tests (like Bonferroni or Tukey’s) will determine specific differences.

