### Methods in analysis to handle protocol non-adherence and any statistical methods to handle missing data {20c}

To comprehensively assess the impact of the devices on delaying myopia onset, we will conduct data analyses using both the Intention-to-Treat (ITT) analysis as the primary result and the Per-Protocol (PP) analysis as the secondary result, along with appropriate handling of missing data in both processes.

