#### ITT analysis (primary result)

The ITT analysis will be carried out to reflect the real-world application effect of the devices in preventing myopia onset. In case a participant drops out or has missing data during the follow-up period, we will use the Last Observation Carried Forward (LOCF) method. This ensures that all randomly assigned participants are retained in the analysis, maintaining the integrity of the randomization and providing a comprehensive view of the overall effect of the devices in a real-life scenario.

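### Two unranked missing-data rules, LOCF and multiple imputation, are set for the same primary ITT analysis, and LOCF counts children lost while still non-myopic as never myopic

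*Protocol article*

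**What the plan says.** Three places in the protocol article deal with missing outcome data.

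- **ITT analysis (primary result), under {20c}:** "In case a participant drops out or has missing data during the follow-up period, we will use the Last Observation Carried Forward (LOCF) method". The section adds that all randomised children are thereby retained. {20c} opens with its purpose: "To comprehensively assess the impact of the devices on delaying myopia onset". It does not name spherical equivalent (SE) or axial length (AL).
- **Statistical methods {20a}, primary-outcome paragraph:** "Missing data will be addressed using multiple imputations by chained equations under the assumption of data missing at random (MAR"). The ITT population here is narrower, "which is defined as all randomized participants with at least one post-baseline measurement". Sensitivity analyses for outliers, nonadherence and loss to follow-up are planned but not specified.
- **Retention {18b}, item 3:** for a child who cannot be reached, "the last available data will be included in the analysis, and the participant will be considered as missing for subsequent follow-up points".

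For the secondary outcomes, {20a} says "The change in spherical equivalent progression over time will be analyzed using a repeated measures mixed-effects model", and that AL change "at each follow-up will be analyzed using a repeated measures mixed-effects model or an analysis of covariance (ANCOVA) for longitudinal data".

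On timing, {18a} says "Cycloplegic measurements will be performed at baseline, the 6-month follow-up, and the 12-month follow-up to assess the primary outcome". Table 1 adds AL at month 3 and schedules refraction without cycloplegia at that visit.

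**The concern.** LOCF and multiple imputation are different primary analyses and can give different answers from the same data. With both standing, the choice could be made after the data are seen.

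LOCF also suits this endpoint badly. Onset accumulates over the year, and the endpoint is judged once, at 12 months. A child seen at month 6, not yet myopic and then lost has been observed for half the risk period but is scored as having completed it free of myopia. A child lost before month 6 has no cycloplegic value after baseline and, by the entry criteria, carries a non-myopic one. Every such child whose eyes would have crossed the threshold is miscounted, always towards no event. A child already myopic at month 6 keeps that classification.

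SE and AL would raise the same problem if LOCF were applied to them, because both change throughout the year.

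**Working it through.** **Inputs from the protocol article.** Onset of 54% (control) and 21% (intervention); 20% anticipated dropout; 64 children per arm; cycloplegic refraction at baseline, 6 and 12 months. The article gives no loss by visit or by arm and no SE or AL progression rates, so those are assumptions below.

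**1. Primary outcome, equal loss after month 6.** Assume constant hazard. Then 6-month incidence = 1 − √(1 − 12-month incidence).
- Control: 1 − √0.46 = 32.2%
- Intervention: 1 − √0.79 = 11.1%

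Under LOCF with random loss L after month 6, observed proportion = (1 − L) × p12 + L × p6. At L = 0.20:
- Control: 0.80 × 54.0 + 0.20 × 32.2 = 49.6%
- Intervention: 0.80 × 21.0 + 0.20 × 11.1 = 19.0%
- Difference: 30.6 points instead of 33.0, a loss of 2.4 points

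For scale, the standard error of the difference with 64 per arm is √[(0.54 × 0.46 + 0.21 × 0.79)/64] = 8.0 points.

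**2. Primary outcome, outer case.** If all 20% were lost before month 6 and carried the baseline value, the difference would be 0.80 × 33.0 = 26.4 points.

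**3. Primary outcome, no true effect and unequal loss.** Take 54% onset in both arms, with 8% control and 20% device loss after month 6.
- Control: 0.92 × 54.0 + 0.08 × 32.2 = 52.3%
- Device: 49.6%, as in step 1
- False benefit: (0.20 − 0.08) × (54.0 − 32.2) = 2.6 points

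**4. SE and AL, only if LOCF reaches them.** With steady change, a child lost after month 6 contributes half the annual change. Equal loss L therefore multiplies the 12-month difference by 1 − L/2:
- L = 10%: 5% shrinkage
- L = 20%: 10% shrinkage

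To express this in dioptres, assume baseline SE uniform from −0.50 to +0.75 D and a normal annual shift with SD 0.5 D. Solve the mean shift so that onset is 54% and 21%. The means are 0.69 and 0.12 D, a difference of 0.57 D.
- Equal 20% loss: 0.20 × 0.57/2 = 0.057 D. Across 12 settings of baseline shape, SD and half-year pattern the range is 0.04 to 0.06 D.
- No true effect (0.69 D in both arms), 8% control and 20% device loss: (0.20 − 0.08) × 0.69/2 = 0.041 D of false benefit.

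For scale, the standard error of the SE difference is 0.5 × √(2/64) = 0.088 D.

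**5. Direction of bias.** For SE, the shrinkage is (Lc × mc − Ld × md)/2, where Lc and Ld are the control and device loss rates and mc and md the mean annual shifts. It turns into overstatement of benefit once Ld/Lc exceeds mc/md. That ratio depends on the true effect:
- 54% versus 21% onset: 0.69/0.12 = 5.8
- 54% versus 40% onset: 0.688/0.465 = 1.5
- No effect: 1.0

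**The case against.** The strongest reply is that {20c} concerns myopia onset, and that {20a} gives SE its own repeated-measures model and AL a mixed model or longitudinal ANCOVA. A reader might infer that the plan applies LOCF to SE and AL. The documents do not establish this. The LOCF sentence is not limited to one outcome, but its section names only onset. The SE and AL figures above are therefore conditional. The conflict over the primary outcome is not, because both rules are stated for it.

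A reader might also infer that LOCF is safely conservative because equal loss shrinks the effect, or that only a several-fold excess of device-arm loss could do harm. Step 5 shows that this rests on 54% versus 21% being true. Those rates come from a retrospective atropine study, and the Discussion concedes that no study of similar equipment was available. With no effect, any excess device-arm loss favours the device.

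It is tempting to say that a child lost between months 3 and 6 has an SE change of exactly zero. That holds for onset, which is defined on cycloplegic refraction. For SE change the text does not say whether the non-cycloplegic month-3 refraction could be carried forward.

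Nor does the retention section say that follow-up stops when a child switches treatment. It mentions collecting data before the switch, and {11b} keeps such children in the study and in the ITT analysis.

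The planned sensitivity analyses for loss to follow-up are a real mitigation. They do not say which rule is primary. A separate analysis plan could add detail, but this is a contradiction within the article, not an omission.

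**Conclusion.** The point holds as a minor one. The article sets two incompatible rules for its primary ITT analysis, and one of them systematically undercounts onset among children lost to follow-up.

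Under constant hazard and 20% loss per arm after month 6, the planned difference falls from 33.0 to 30.6 points, about 0.3 of its standard error (2.4/8.0). With no true effect, 8% versus 20% loss would produce about 2.6 points of false benefit. For SE and AL the effect is conditional on LOCF being applied: 10% shrinkage at 20% equal loss, about 0.06 D in the assumed base case and below one standard error.

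These sizes depend on assumed hazard, progression, and timing and split of loss. The contradiction does not.

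**What to change.** - **ITT analysis (primary result):** replace LOCF with the multiple imputation of {20a}, including the month-6 SE and the AL values in the imputation model, as the single rule for the primary outcome. Keep LOCF at most as a labelled sensitivity analysis.
- **SE and AL:** state that both are analysed by the mixed model on all observed visits, without LOCF. For AL this means choosing the mixed model over the ANCOVA alternative.
- **Retention {18b}, item 3:** say that all observed visits are kept and later visits are treated as missing.

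The cost is a few sentences and slightly more analysis work. The methods are already in {20a}, and no visit is added. Recruitment ended in September 2025, so 12-month visits run to about September 2026. The rule should be fixed before the data are analysed.

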#### PP analysis (secondary result)

The PP analysis will be employed as a secondary result to focus on the effect among those participants who strictly adhered to the use of the devices and followed the study protocol precisely. Only those subjects who completed all the required procedures, used the devices as instructed (e.g., for the specified duration and frequency), and attended all the follow-up visits without any major deviations from the protocol will be included in this analysis. To maintain the purity of the analysis, we will use direct exclusion to handle the missing data.

In conclusion, by utilizing both ITT and PP analyses with appropriate handling of missing data, we expect to obtain a comprehensive and in-depth understanding of the effect of the DIST on delaying myopia onset in pre-myopic children from different perspectives, which will contribute to a more robust and reliable evaluation of the efficacy of these devices in this context.

### Plans to give access to the full protocol, participant-level data, and statistical code {31c}

In our clinical research, we have well-defined plans for sharing important study materials to ensure transparency and reproducibility.

Firstly, the full protocol of our study will be published in the Trials. Additionally, when the research is concluded and the corresponding article is published, the full protocol will also be attached as Supplementary materials at the end of the main text.

Secondly, regarding the raw data, we will make it available on the data platform of our hospital’s clinical research center. However, this will take place after the official publication of the research article. To access the raw data, interested parties are required to fill out a corresponding application form. They can then submit the application to the corresponding author for review. During this process, strict ethical and privacy safeguards are in place. The raw data will be anonymized to protect the identities of the participants by removing or encrypting personal identifiers such as names, addresses, and social security numbers. This ensures that while enabling the sharing of valuable data for further research and verification purposes, the privacy rights of the participants are duly respected.

## Oversight and monitoring

### Composition of the coordinating center and trial steering committee {5d}

In this single-center clinical trial, the coordinating center is the hospital’s Clinical Research Center. The trial steering committee plays a key role, composed of 2 hospital senior ophthalmology experts, 3 statistics experts (1 external), the project leader, and the sponsor’s leader. It is responsible for determining the full trial protocol, reviewing progress, and setting endpoints.

The Ethics Committee safeguards ethical aspects. The Endpoint Adjudication Committee, with 2 experts, ensures endpoint accuracy. And the Data Management Team, having 2 admins and 2 quality control staff, maintains data quality.

The project research team consists of clinical ophthalmologists, laboratory researchers, and research assistants from the sponsor. They jointly handle tasks like participant recruitment, intervention implementation, outcome evaluation, data management, and analysis. Each task has an experienced leader. The steering committee oversees the whole study, while the research team holds monthly meetings to discuss progress and solve trial-related issues. Together, these components work in harmony to support the trial’s success and ensure its scientific integrity and high quality.

